For all of these scans, the participant only has to lie quietly and remain still in the scanner. Each scanning session (consisting of a total of two 10 minute scans) takes a little under 25 minutes to complete and is considered completely non-invasive. The only discomfort is the requirement that subjects lay still in the scanner for the duration. All patient participants complete a general health questionnaire (PHH), the short form of McGill Pain Questionnaire (sf-MPQ), the Western Ontario and McMaster Osteoarthritis Index (WOMAC), and the Beck Depression Index (BDI) at screening, the time of entry (baseline visit), and at the final scanning visit (visit 5). Only the WOMAC will be completed on interim visits three and four.

Healthy control participants will participate in part two of the study only. They will be asked to complete the PHH only at the screening visit (to make sure that there are no potential physical or mental comorbidities or confounding medications). They will be asked to personally complete the BDI at all visits, and they will have the same number and types of scans as OA participants.

All participants will also have the choice of completing an optional visit at the very end of the study that involves answering questions in an open-ended interview and completing a set of new questionnaires that supplement this interview. OA participants will be asked a series of questions about their chronic pain, mood, medical history, and medical beliefs which, depending upon how detailed their responses are, will last 30 minutes to an hour. After the interview, OA participants will be asked to fill out the Chronic Pain Acceptance Questionnaire (CPAQ), the Pain Sensitivity Questionnaire (PSQ), the Perceived Sensitivity to Medicine Scale (PSM), the Five-Factor Personality Index (NEO-FFI), and the Life Orientation Test, Revised version (LOT-R). Healthy participants will be asked a series of questions, most of which are the same as those for the OA and some of which are different and ask about acute painful experiences instead of chronic pain. There are less questions for healthy participants than OA participants, so depending upon how detailed their responses are, healthy participant interviews will last 20-40 minutes. After the interview, healthy participants will be given the PSQ, PSM, NEO-FFI, and LOT-R.

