#### **PART TWO:**

Visit 1: Pre-Screening: Medical history, physical exam, questionnaires

Visit 2: Screening: blood test, pregnancy test for women of childbearing potential, MRI scan

Visit 3: Randomization (within 2 weeks of screening): randomization and initiation of study drug/placebo and rescue medications (30 mg/day)

Visit 4: Interim Visit (week 1  $\pm$  3 days): evaluation of clinical status, increase dose of duloxetine/placebo to 60 mg/day

Visit 5: Interim Visit (week 6  $\pm$  7 days): evaluation of clinical status

Visit 6: Final Interim Visit (week 16  $\pm$  14 days): evaluation of clinical status, MRI scan, begin tapering the dose study drug/placebo over a 1 to 2 week period, collect empty bottles and unused rescue medication

Follow-up: Phone Call (week 18 at maximum): evaluation of clinical status, verify that the study drug/placebo was successfully stopped

Optional Visit: Interview (week 20 and beyond): ask questions about mood, pain, and health history, questionnaires

OA participants will receive compensation for completing visits 1, 2, 3, 4, 5, 6, and Optional. Healthy controls will receive compensation for visits 2, 6, and Optional. Compensation will be given to participants either at the end of each visit (if the amount is \$50 or under) or in the form of a check a few weeks later (if the amount is greater than \$50). Compensation is as follows:

Visit 1 (Pre-Screening): \$25 for OA; N/A for healthy controls

Visit 2 (Screening, with MRI): \$50 for all participants

Visit 3 (Randomization): \$25 for OA; N/A for healthy controls

Visit 4 (Interim): \$25 for OA; N/A for healthy controls

Visit 5 (Interim): \$25 for OA; N/A for healthy controls

Visit 6 (Final Interim, with MRI): \$50 for all participants

Follow-up (Phone Call): \$0 for OA; N/A for healthy controls

Optional Visit (Interview): \$25 for all participants

In addition, for both phases of the study, all participants will receive additional compensation for transportation and parking (if applicable), and this compensation is available for all visits (1 through 6, and optional if applicable). We will reimburse individuals up to \$20 in various travel expenses, such as CTA fares or driving costs, and we will validate their parking stickers if they park in the garage at [name] or at [name].

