Treatment begins at 30 mg once daily for 1 week, to allow patients to adjust to the medication before increasing to 60 mg once daily. Some patients may respond to the starting dose. There is no evidence that doses greater than 60 mg/day confer additional benefit, even in patients who do not respond to a 60 mg dose, and higher doses are associated with a higher rate of adverse reactions. Before discontinuing patients, a gradual reduction in the dose rather than abrupt cessation is recommended. Patients will take 30 mg once daily for 1 week before cessation.

Duloxetine should be swallowed whole and should not be chewed or crushed, nor should the capsule be opened and its contents sprinkled on food or mixed with liquids. All of these might affect the enteric coating. Duloxetine can be given without regard to meals.

Duloxetine's matching placebo pellets are filled into size 1 blue/blue capsugel shells. Overall ingredients: empty gelatin capsules and Nu-Pareil sugar spheres. The matching placebo has a stability of 60 months with minimum allowable storage temperature limits: 15 degrees C/max allowed 25 degrees C. Do not refrigerate or freeze. Route of administration is oral.

Duloxetine is commercially available. Duloxetine and its matching placebo is provided free of charge by the Neuroscience Division of Lilly USA, LLC.

Duloxetine contains a black box warning for Suicidality (suicidal thoughts and/or self-harmful behavior). There is an increased risk of suicidality in children, adolescents, and young adults with major depressive or other psychiatric disorders.

The most common adverse events (happening in more than 5 of 100 people) are:

- Nausea
- Constipation
- Diarrhea
- Decreased appetite
- Dry mouth
- Sweating or night sweats
- Dizziness
- Headache
- Tiredness

- Weakness
- Drowsiness

Less common adverse events (happening in at least 2 of 100 people) include the following:

- Vomiting
- Stomach and/or abdominal pain
- Increased urination
- Difficulty urinating
- Blurred vision
- Fast or irregular heartbeat
- Weight changes
- Tremors (uncontrollable shaking of a part of the body)
- Changes in sexual desire or ability (see section below)
- Yawning
- Hot flashes
- Acid reflux
- Fever
- Hoarseness or sore throat
- Muscle pain or cramps
- Flu-like symptoms
- Seasonal allergy-like symptoms
- Upper respiratory infection
- Change in taste
- Anxiety or agitation
- Tingling at the fingers or toes, or general differences in sensation
- Rash
- Hives
- Itching

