**PART TWO:**

- Visit 1: **Pre-Screening**. Medical history, physical examination, patient-reported outcome (PRO) battery of instruments (includes: a general health questionnaire (PHH), the short form of McGill Pain Questionnaire (sf-MPQ), WOMAC, and the Beck Depression Index (BDI)), the Pain detect questionnaire, and the Pain catastrophizing scale (PCS)
- Visit 2: **Screening/Baseline Scan**. Basic chemistry panel and complete blood count (CBC), pregnancy test for females of child-bearing potential, MRI scans
- Visit 3: **Randomization**. (Week 0) WOMAC, dispense Duloxetine/placebo (at 30mg/day) and rescue medications, collect information on concomitant medications
- Visit 4: **Interim Visit**. (Week 1 ± 3 days) Dispense drug/placebo (increase dose of duloxetine/placebo to 60 mg/day), WOMAC, collect AEs and concomitant medication information
- Visit 5: **Interim Visit**. (Week 6 ± 7 days) Dispense drug/placebo (same dose as in Visit 3), WOMAC, BDI, collect AEs and concomitant medication information
- Visit 6: **Interim Visit**. (Week 16 ± 14 days) Dispense drug/placebo (begin to gradually reduce dose via a down-titration of 30mg for 1 week), MRI scans, PRO battery, collect AEs and concomitant medication information; collect unused rescue medications and empty duloxetine/placebo bottles
- Follow-up: **Phone call**. (Week 18 maximum) Collect AEs and concomitant medication information, verify that participant has successfully stopped the drug/placebo

Optional: **Interview** (Week 20 and beyond): Ask a series of open-ended questions about participants' experiences with pain, overall mood and personality, and medical history; give questionnaires about personality and pain/medical beliefs and expectations

Control participants will only complete visits 2 and 6. More specifically, they will only complete the PHH (once during screening) and the BDI (at all visits). Urine dipstick pregnancy tests will only be done in healthy controls if the participant is a woman of child-bearing potential. No blood will be drawn. Control participants also have the choice of completing an optional visit at the very end of the study that involves answering questions in an open-ended interview and completing a set of new questionnaires that supplement this interview.

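### The Visit 5 dispensing line points to the 30 mg/day starting dose, contradicting the 60 mg/day regimen fixed elsewhere in the protocol

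*Protocol*

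**What the plan says.** The dose is set in three places in the protocol.

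- **Study Procedures (more detailed), Part Two.** Visit 3, at week 0: "dispense Duloxetine/placebo (at 30mg/day) and rescue medications". Visit 4, at week 1: "Dispense drug/placebo (increase dose of duloxetine/placebo to 60 mg/day". Visit 5, at week 6: "Dispense drug/placebo (same dose as in Visit 3), WOMAC, BDI". Visit 6, at week 16: "begin to gradually reduce dose via a down-titration of 30mg for 1 week".
- **Study Drug.** Patients take 30 mg once daily for the first week, "to allow patients to adjust to the medication before increasing to 60 mg once daily". The lower dose returns only at the end: "Patients will take 30 mg once daily for 1 week before cessation".
- **The shorter Part Two visit schedule under Study Design.** It starts at 30 mg/day at Visit 3, moves to 60 mg/day at Visit 4 and mentions only a clinical evaluation at Visit 5. At Visit 6 it says to "begin tapering the dose study drug/placebo over a 1 to 2 week period".

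The Study Design text on questionnaires uses a different visit numbering. It numbers the interim visits three and four, and it places the last questionnaires "at the final scanning visit (visit 5"). In both visit lists the interim visits before the final scan are 4 and 5, and the final scan is at Visit 6.

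**The concern.** Taken at face value, the Visit 5 line returns every patient to the starting dose at week 6, after only five weeks at 60 mg/day. No other part of the protocol provides for this.

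The line matters because it is an operative dispensing instruction in the list that staff would naturally work from. It covers the last supply before the final scan, nominally 10 of the 16 treatment weeks. The primary hypothesis concerns four months of duloxetine against placebo, and the secondary hypothesis ties pain relief to brain change, so both depend on the exposure delivered in the active arm. Drug is also held and logged separately at two sites. If one site followed the detailed list and the other the Study Drug section, the active dose would differ by site.

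**Working it through.** The plan states no cumulative dose, so there is no figure to reproduce. The check has two parts.

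**1. The texts side by side (Part Two)**

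| Time | Detailed list, read literally | Study Drug section | Short visit schedule |
|---|---|---|---|
| Visit 3, week 0 | 30 mg/day | 30 mg/day | 30 mg/day |
| Visit 4, week 1 | 60 mg/day | 60 mg/day | 60 mg/day |
| Visit 5, week 6 | dose of Visit 3, so 30 mg/day | 60 mg/day | no change stated, so 60 mg/day |
| Visit 6, week 16 | begin reduction | 30 mg for 1 week, then stop | begin taper over 1 to 2 weeks |

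The explicit conflict is with the Study Drug section. The short schedule gives no dose at Visit 5. Its 60 mg/day follows from the increase at Visit 4 and the absence of any reduction before Visit 6.

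The literal reading also fails against the next line of its own list. If patients were already on 30 mg/day at Visit 6, a step to 30 mg would reduce nothing, and a step down by 30 mg would leave nothing to dispense. The Visit 6 line makes sense only if patients arrive on 60 mg/day.

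**2. Size if the line is followed literally (active arm)**

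Inputs, from the Part Two visit list: Visit 4 at day 7 (± 3 days), Visit 5 at day 42 (± 7 days), Visit 6 at day 112 (± 14 days). Full adherence is assumed, and dose is counted up to Visit 6.

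- Intended dose = 30 × V4 + 60 × (V6 − V4)
- Literal dose = 30 × V4 + 60 × (V5 − V4) + 30 × (V6 − V5)
- Shortfall = 30 × (V6 − V5)

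Nominal visits:

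- Intended: 7 × 30 + 105 × 60 = 6,510 mg, mean 6,510/112 = 58.1 mg/day
- Literal: 7 × 30 + 35 × 60 + 70 × 30 = 4,410 mg, mean 4,410/112 = 39.4 mg/day
- Shortfall: 70 × 30 = 2,100 mg, and 2,100/6,510 = 32.3%

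Visit-window extremes:

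| Case | V4, V5, V6 (day) | Affected stretch | Intended dose | Shortfall |
|---|---|---|---|---|
| Smallest | 4, 49, 98 | 49 days (7 weeks) | 4 × 30 + 94 × 60 = 5,760 mg | 1,470 mg, 25.5% |
| Largest | 10, 35, 126 | 91 days (13 weeks) | 10 × 30 + 116 × 60 = 7,260 mg | 2,730 mg, 37.6% |

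Weeks at 30 mg, counting a 1-week taper: intended 1 + 1 = 2, literal 1 + 10 + 1 = 12. If the 2-week taper allowed by the short schedule were spent at 30 mg, these would be 3 and 13.

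**Likely origin.** The questionnaire text in Study Design places the interim visits and the final scan one number lower than both visit lists do. Shifting by one, the older Visit 3 would be the present Visit 4, where the dose rises to 60 mg/day. The Visit 5 reference would then once have been correct. This is an inference, and the contradiction stands without it.

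**The case against.** The strongest reply is that the intended dose is never in real doubt. The regimen is written out in the Study Drug section, the 60 mg/day step appears in both visit lists, and the Visit 6 line presumes it. On this view the defect is one wrong digit in a cross-reference. The 32% arises only if staff follow a single parenthesis and disregard everything around it, and no sample-size, endpoint or analysis statement depends on the line.

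Most of this is fair. The intent is recoverable, and the exposure figures describe what the text orders, not what patients received. It does not make the line harmless, because a dispensing instruction is read on the day by whoever hands out the bottles, and a wrong dose there is more than a slip in background text.

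Two smaller objections also stand. First, the stale-number explanation is not proven. The older numbering appears without weeks or doses, and its questionnaires differ from the current ones: it has only the WOMAC at interim visits, whereas the present Visit 5 adds the BDI. Second, the site dispensing instructions are not in the protocol and may already say 60 mg/day.

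**Conclusion.** The concern holds. The Visit 5 line is wrong as written, contradicts the Study Drug section, and is inconsistent with the visits before and after it in the same list. The intended dose is 60 mg/day.

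The consequence is conditional. Literal compliance would halve the daily dose from week 6 to week 16 and cut the cumulative dose to the final scan by 32% at nominal visits, or 25.5% to 37.6% across the windows, assuming full adherence. If 60 mg is dispensed as intended, the loss is zero. The protocol gives no dose-response figure, so an effect on grey matter or pain cannot be sized. The error should be corrected, but it is not a flaw in the trial's design.

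**What to change.** - In the detailed Part Two list, change Visit 5 to dispense the Visit 4 dose, stated as 60 mg/day. This alone removes the contradiction: 1 week at 30 mg and 15 weeks at 60 mg before the taper, 6,510 mg at nominal visits.
- State the dose in mg at every dispensing visit, so that no dose rests on a visit number.
- Align the questionnaire text in Study Design with the visit lists: interim visits 4 and 5, final scan at Visit 6.
- Check the dispensing instructions at both sites against the corrected line.

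The cost is a wording correction in two places and a check of site documents. No new patients, data or analyses are needed.

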### ***Recruitment, Selection, and Discontinuation of Subjects***

#### Study Population:

Patients with chronic (>1year) symptoms of knee osteoarthritis

#### Recruitment and Enrollment Design

Participants will be recruited from an osteoarthritis patient database available through two sites. The first site is the Rehabilitation Institute of Chicago (RIC), which the study doctor ([name]) has access to and the second site is the Northern Ohio Neuroscience, LLC, which the study doctor ([name]) has access to. They will be contacted via telephone to see if they are interested, and if so, to see if they qualify for the screening visit. All participants will complete a screening visit with either [name] or [name] to determine if they are eligible to continue in the study. Eligibility will be based on the inclusion and exclusion criteria stated below, and these criteria will be measured through a physical exam, blood tests (to screen for abnormal chemistry panels and complete blood counts, as well as pregnancy if applicable), answers participants give in their questionnaires and MRI screening forms, as well as those regarding their medical history and current medications.

Control participants will undergo a similar screening visit, except that they do not need to complete a physical exam or blood tests. If the participant is a woman of child-bearing age, then she must give urine to be used for a urine dipstick pregnancy test).

Participants will be given a written, informed consent form during the screening visit, and if they are eligible and want to participate, they will be invited to come back for subsequent visits. Note that healthy controls will only complete two visits (screening/baseline scan and the final visit involving an MRI scanning session).

Number of Subjects:

\* 80 participants with chronic osteoarthritis in their knee (20 in phase I and 60 in phase II. The 20 in phase I will all receive placebo. In phase II, 30 will receive the study drug; 30 will receive placebo)

\* 25 healthy controls

Inclusion and exclusion criteria:

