Brain image data collection and analysis is done under [name] supervision, which will be performed double blinded. Brain scan data will be transferred to [name]'s lab where the automated brain morphometric analyses are performed. We contrast brain morphology using a 2-way analysis of variance, factor one is group (patients treated with drug, with placebo, and healthy controls), and factor two is repeat measure time of scan. A secondary analysis will involve correlating brain regional changes to pain (VAS score from sf-MPQ) and the other questionnaire outcomes.

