### Study Drug

Cymbalta® (Duloxetine Delayed-Release Capsules) is a selective serotonin and norepinephrine reuptake inhibitor (SSNRI) for oral administration. Its chemical designation is (+)-(S)-N-methyl-γ-(1-naphthoxy)-2-thiophenepropylamine hydrochloride. The empirical formula is C18H19NOS·HCl, which corresponds to a molecular weight of 333.88. The structural formula is:

[figure not shown]

Duloxetine hydrochloride is a white to slightly brownish white solid, which is slightly soluble in water. Each capsule contains enteric-coated pellets of 22.4, 33.7, or 67.3 mg of duloxetine hydrochloride equivalent to 20, 30, or 60 mg of duloxetine, respectively. These enteric-coated pellets are designed to prevent degradation of the drug in the acidic environment of the stomach. Inactive ingredients include FD&C Blue No. 2, gelatin, hypromellose, hydroxypropyl

methylcellulose acetate succinate, sodium lauryl sulfate, sucrose, sugar spheres, talc, titanium dioxide, and triethyl citrate. The 20 and 60 mg capsules also contain iron oxide yellow.

Although the exact mechanisms of the antidepressant, central pain inhibitory and anxiolytic actions of duloxetine in humans are unknown, these actions are believed to be related to its potentiation of serotonergic and noradrenergic activity in the CNS.

Duloxetine is stored at 25°C (77°F); excursions permitted to 15-30°C (59-86°F). For Chicago Site: Study drug will be maintained in a locked cabinet in a locked room in Abbott Hall. A drug accountability log will be completed each time drug is dispensed or returned and will be maintained by the study coordinator. For Ohio Site: Study drug will be maintained in a locked cabinet in a locked room in NON's office complex. A drug accountability log will be completed each time drug is dispensed or returned and will be maintained by the [name], the site's study coordinator and [name], the site's study physician.

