### ***Randomization and Blinding Design***

For the first part of the study (Phase I), all patients will receive placebo. The design is single blinded; the participants will not know whether they are receiving active drug or placebo. The researcher, however, will know that they are all receiving placebo.

A one-to-one randomization will be used for drug vs. placebo in the second part of the study (phase II). The healthy controls will be matched to the treatment group by age, gender, and education. In addition, the double blind will be maintained throughout all study procedures.

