#### Sample Size Considerations:

Effect size: Given that the design is a within subject repeat measures analysis of variance, the overall variance should be about half of that we had originally anticipated. In fact, two recent studies were able to show significant restoration of grey matter in n=10 patients with such a design. However, in those two studies the pain relief was complete for many months. Here we expect a smaller decrease in pain (between 10-20mm on VAS scale from baseline) and, as a result, we have increased the sample size of the population treated with drug three times. Moreover, assuming that pain relief will be less in the placebo group, inclusion of this arm into the study should strengthen the power of the study. The healthy normal subjects tested at two equivalent time points is necessary to rule out that the observed results are scanner artifacts. In the normal subjects we specifically test that in the same time period and using the same scanner we observe no significant, or minimal increased atrophy (0.75 cc increase in atrophy, in the direction opposite of what we expect to see with drug treatment). Moreover, since we already have results regarding brain regions where atrophy is observed in OA, we can perform brain region-specific directed contrasts between the groups, if necessary. Overall, this design should give us enough power to test the primary and secondary hypotheses. It should be noted, however, that this is an exploratory study, and there is no statistical justification to our proposed sample size.

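### Part Two runs at two sites, but the stated allocation and model leave site out and the place of scanning for Ohio patients is not given: a modest loss of precision that is cheap to avoid

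*Protocol*

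**What the plan says.** - **Sites.** Recruitment and Enrollment Design: "Participants will be recruited from an osteoarthritis patient database available through two sites". These are one centre in Chicago and one in Ohio, each with its own study doctor. Ohio is an operating treatment site and not only a source of referrals: "For Ohio Site: Study drug will be maintained in a locked cabinet in a locked room", with its own accountability log (Study Drug).
- **Allocation.** Randomization and Blinding Design: "A one-to-one randomization will be used for drug vs. placebo in the second part of the study (phase II". The arm sizes are given as "In phase II, 30 will receive the study drug; 30 will receive placebo". No stratification factor is named.
- **Controls.** The 25 healthy controls are matched as follows: "The healthy controls will be matched to the treatment group by age, gender, and education". Site is not among the factors.
- **Model.** The image-analysis paragraph after the Part Two visit schedule sets a two-way analysis of variance: "factor one is group (patients treated with drug, with placebo, and healthy controls), and factor two is repeat measure time of scan". Statistical Analysis lists the corrections: skull size or whole-brain volume, age and sex.
- **Scanner.** Sample Size Considerations bases the control check for scanner artefact on observations made "in the same time period and using the same scanner". Safety Assessment names one imaging centre, and Potential Problems or Pitfalls speaks of a single MR scanner. No section says where Ohio patients are scanned.

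**The concern.** The protocol fixes an allocation ratio, a model, a list of corrections and a one-scanner premise, and reconciles none of them with its second site. The endpoint is a small change in gray matter: the protocol expects 0.75 cc of ageing loss over the treatment period. If measured change differed between sites, an uneven site mix would move the drug-placebo difference in the trial actually run, and the unmodelled site variance would stay in the error term. If some patients were scanned on another machine, the control check would say nothing about drift on it. The drug-arm size is reasoned as three times the 10 patients of earlier studies, and the same section says that the sample size has no statistical justification. There is therefore no stated margin to absorb a loss.

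**Working it through.** **Inputs from the protocol:** two sites; 30 drug and 30 placebo; factors group and time; corrections without site; 0.75 cc ageing loss (2.5 × 0.3). The only sample-size figure reproduces as plain arithmetic: 3 × 10 = 30. No power, alpha or SD is stated.

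**Assumptions, because the protocol gives no figure:** Ohio share *f* of 20-50%; site difference *g* in mean change, in within-site SDs of change, from 0 to 2; two-sided alpha 0.05; true effect 0.723 SD, chosen because it gives 80% power at 30 per arm by the normal approximation.

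**1. What reaches the group-by-time contrast.** Write baseline volume as a + o and follow-up volume as a + o + c + h. Here a belongs to the patient, o is a constant site or scanner offset, c is the patient's own change and h is the site's mean shift in change. The change is c + h. The offset o cancels, and only h remains. If a patient were scanned on different machines at the two visits, o would no longer cancel.

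**2. Chance imbalance without stratification.** The SD of the between-arm gap in Ohio share is √(f(1−f) × 2/30). The probabilities below are exact (hypergeometric) for a fixed 30/30 split.

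| Ohio share | 1.96 × SD | P(gap ≥ 10 points) | P(gap ≥ 20 points) |
|---|---|---|---|
| 20% (12 of 60) | 0.20 | 0.33 | 0.10 |
| 30% (18 of 60) | 0.23 | 0.40 | 0.16 |
| 50% (30 of 60) | 0.25 | 0.44 | 0.20 |

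At the 95% limit, each 1 cc site difference in mean change shifts the contrast by 0.20-0.25 cc.

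**3. Precision.** Leaving site out multiplies the residual SD of change by √(1 + f(1−f)g²). At f = 0.5 and g = 0.5 this is √1.0625 = 1.031; at g = 1 it is √1.25 = 1.118. The last two columns come from 40,000 simulated trials per setting, with unstratified allocation and change as the outcome.

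| f | g | SD factor | Power, normal approx., no site | Simulated, no site | Simulated, site in model |
|---|---|---|---|---|---|
| 0.2 | 0 | 1.000 | 0.800 | 0.790 | 0.783 |
| 0.2 | 0.5 | 1.020 | 0.784 | 0.770 | 0.779 |
| 0.2 | 1 | 1.077 | 0.739 | 0.725 | 0.778 |
| 0.3 | 0.5 | 1.026 | 0.780 | 0.765 | 0.779 |
| 0.3 | 1 | 1.100 | 0.721 | 0.707 | 0.780 |
| 0.5 | 0.5 | 1.031 | 0.776 | 0.760 | 0.777 |
| 0.5 | 1 | 1.118 | 0.707 | 0.691 | 0.781 |

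At g = 2 simulated power without site falls to 0.49-0.58, and with site it stays near 0.78. By the normal approximation, restoring the same power at g = 1 takes 35-38 per arm instead of 31 (30.006 rounded up).

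**4. Type I error.** Over all settings the simulated rate was 0.049-0.052 without site and 0.049-0.053 with it.

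**The case against.** *The documents point to one scanner.* This stands. Every description of scanning is singular. A reader might infer local scanning in Ohio from the $20 ceiling on travel reimbursement, since two Part Two visits include MRI. That fits poorly with travel to Chicago but proves nothing. A second scanner is a possibility left open by silence, not a fault shown.

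*Site has little way into the outcome.* This stands in part. Morphometry is automated, blinded and done in one laboratory, and a constant offset cancels by step 1. Statistical Analysis is looser, because it contrasts normalised volume between arms without saying that the value is the change. If follow-up volumes alone were compared, constant offsets would count as well. The analysis-of-variance paragraph and the Part Two procedures, however, both specify a comparison of the two time points.

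*The trial stays valid.* This stands. A reader might take inflated error to mean a biased contrast or an excess of false positives. Step 4 shows neither. Chance imbalance is already reflected in the standard error, so steps 2 and 3 describe one cost from two sides and must not be added.

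*The size is assumed and the 1 cc scenario is severe.* This stands. It exceeds the whole expected ageing loss of 0.75 cc. Against the potential reversal under complete relief, which the Background puts at 6.0 − 0.75 = 5.25 cc (its own factors, 1.5 × 5, give 7.5 cc, which widens the gap), a shift of 0.20-0.25 cc is small.

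*Strata and covariates may be in an unseen plan.* This stands in part. An analysis plan can add a site term. It cannot add stratification once patients have been randomised, and the place of scanning is a matter of conduct that the protocol should state.

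**Conclusion.** The point holds as a precision and clarity matter of modest size. Site is absent from the allocation and the model that the protocol describes, and the one-scanner premise is not squared with the Ohio site. At 30 per arm a site gap of at least 10 points has probability 0.33-0.44 for Ohio shares of 20-50%. The cost in power is about 2-3 points at a site difference in change of 0.5 SD and becomes material near 1 SD (power about 0.69-0.74). It is nil if the sites do not differ in change. Site share and site effect are assumptions throughout. The documents do not support a finding of bias, of inflated type I error or of a second scanner. In a trial that calls itself exploratory this is a cheap improvement and no threat to validity.

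**What to change.** 1. Stratify the Part Two allocation by site.
2. Include site-by-time in the repeated-measures model, or site as a covariate in a model of the change. A site main effect alone is between-subject and does not adjust the group-by-time contrast.
3. State where Ohio patients and healthy controls are scanned, and require both scans of a participant on the same scanner.
4. If more than one scanner is used, add scanner-by-time and limit the control artefact check to the scanner or scanners that the controls used.

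The cost is a two-stratum randomisation list, one degree of freedom in the contrast (58 to 57 for two arms of 30) and a sentence or two of text, with no extra patients or procedures. If the sites do not differ at all, the simulations put the price of the site term at under one point of power (0.786-0.790 without it, about 0.78 with it).
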